### Data Sources and Management

The REDCap platform hosted at UNC Chapel Hill is a HIPAA-compliant web-based platform that will serve as a central repository for data collected by the study team, including administration of ambassador and peer e-consent forms, participant recruitment and enrollment tracking, and collection of screening, appointment results, and survey data. Public health surveillance data obtained from the North Carolina Electronic Disease Surveillance System (under a data sharing agreement with North Carolina DHHS) will be stored in a secure cloud drive and REDCap. We plan to routinely analyze HIV sequences reported to the state and associated case-level epidemiological data to facilitate timely response to clusters within NC DHHS’s Region II (Charlotte).

### Data Analysis

#### Hypothesis

Our principal hypothesis posits that implementing eSNS will increase the uptake of HIV services within the Charlotte region among members of priority networks when compared to the Raleigh region over the same period. By harnessing peer social support networks, eSNS is designed to mitigate structural barriers—including stigma, distrust, limited PrEP knowledge, and difficulties navigating complicated medication logistics—that underlie disparities in HIV prevention and treatment services uptake among members of priority networks engaged by routine partner services (and among our key population). Compared to partner services alone, which is the standard of care intervention in North Carolina and South Carolina, we also hypothesize that enhancing standard SNS with genetic cluster analysis will enable further penetration into priority networks where onward HIV transmission is occurring by identifying a greater number of persons living with undiagnosed HIV that is closely related to HIV in other members of the network.

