**Figure 4. F4:**
[figure not shown]
Schematic overview of enhanced social network strategy (eSNS) intervention among priority networks identified during routine partner services. A. Partner services as routinely delivered by disease intervention specialists (DIS) eliciting contacts (usually sexual or injecting partners) for notification of exposure to HIV. B. Partner services when combined with HIV cluster response, where genetic cluster members who are not virally suppressed are also linked to care services. C. Standard social network strategy (SNS), where potential network recruiters (ambassadors) are identified from a population of interest, then coached to reach out to network members (peers) for HIV testing. D. eSNS, which combines all 3 strategies. SOC: standard of care; PrEP: pre-exposure prophylaxis.

Following the completion of routine partner services activities (contact tracing and voluntary partner notification), potential community ambassadors will be identified from among members of Priority Networks reached through partner services, including index persons and their social and sexual contacts (see Figure 4). DIS coaches will then lead ambassadors through a semistructured coaching session designed to develop an action plan for ambassadors to reach out to and refer their peers—who may be friends or acquaintances, not necessarily sexual or injecting partners—for HIV prevention and care services. Once peers contact the study team, DIS coaches will assist peers in accessing HIV testing, care, or PrEP services.

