#### Effectiveness Evaluation

Intervention effectiveness will be assessed by comparing the 5-county Charlotte region to another urban North Carolina region, Raleigh, with similar demographics (see Figure 1). The metropolitan region surrounding Raleigh has the second-largest population in North Carolina, after Charlotte [47]. The primary effectiveness measures are the number of HIV-negative individuals linked to PrEP and the individuals living with HIV who are linked to care per index person from a priority network. Index persons in the intervention region (Charlotte) priority networks will be compared to index persons in the control region (Raleigh) priority networks, who receive standard-of-care partner services. Partner services are standardized among all North Carolina DHHS Field Service regions [48]. We will use a regression point displacement design (RPDD) [49] to assess the impact of eSNS on trends in our primary effectiveness measures between regions over the intervention period; the effective reproduction number for HIV will also be calculated over this period. Measures will be collected for each region at a preintervention baseline (2 years before), postintervention (6 months after), and during implementation for interim analyses at 6-month intervals. Because state HIV surveillance data is available in both the Charlotte and Raleigh regions from the baseline timepoint to a postintervention timepoint, RPDD provides statistical power to estimate the effect of eSNS when aggregating at a group level (index persons from priority networks) [50].

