Although we adapted our original intervention design to enroll eSNS ambassadors through both routine partner services for index persons from priority networks and through ongoing waves of community-based recruitment, we will calculate the same effectiveness measures for ambassadors enrolled through each source. Only outcomes for ambassadors enrolled through partner services will be included in the RPDD analysis. However, for ambassadors enrolled through both sources, secondary effectiveness measures will also assess the extent to which eSNS penetrates priority networks where HIV transmission is ongoing. Among peers referred by all ambassadors, we will use a combination of study data, state HIV surveillance data, and molecular epidemiology to calculate the proportion of peers living with HIV that has close genetic linkages [42] to a cluster. We will also assess penetration into priority networks by calculating the proportion of newly diagnosed peers who initiate care, proportion of previously diagnosed peers who re-engage in care, the overall positivity among peers who test for HIV, and the proportion of peers testing negative who then initiate PrEP. Selected primary and secondary effectiveness measures are described in Table 1.

**Table 1. T1:** Selected effectiveness measures of the enhanced social network strategy (eSNS) intervention.

Measures and description		Data source
Network Index		
Number of individuals diagnosed with HIV and linked to care per associated index case.^a^		Surveillance data
Number of HIV-negative individuals linked to PrEP^b^ per associated index case.^a^		Surveillance data
Cluster analysis		
Proportion and number of peers living with HIV who are associated with a genetic cluster involving a new HIV diagnosis.		Study and surveillance data
Peers identified with high network bridging scores (betweenness centrality) [51].		Study and surveillance data
Viral suppression		
Number of peers per ambassador previously diagnosed with HIV who are not virally suppressed.		Study and surveillance data
Care and prevention linkage		
Proportion and number of peers newly diagnosed with HIV who initiate care.		Study data
Proportion and number of peers previously diagnosed with HIV who re-engage in care.		Study data
Proportion and number of peers who test negative and initiate PrEP.		Study data
Proportion of positive tests among all peers who test for HIV.		Study data

a Primary effectiveness measures.

b PrEP: pre-exposure prophylaxis.

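### The second hypothesis compares eSNS with partner services on finding undiagnosed, genetically linked HIV, but the plan as described does not test it between regions

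*Protocol article*

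**What the plan says.** The Hypothesis section of the protocol article gives a principal hypothesis on uptake of HIV services, then a second one. The second names its comparator: "Compared to partner services alone, which is the standard of care intervention in North Carolina and South Carolina". It says that "enhancing standard SNS with genetic cluster analysis will enable further penetration into priority networks where onward HIV transmission is occurring", and gives the route: "identifying a greater number of persons living with undiagnosed HIV that is closely related to HIV in other members of the network".

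Under Effectiveness Evaluation, index persons in Charlotte are compared with those in "control region (Raleigh) priority networks, who receive standard-of-care partner services". The regression point displacement design (RPDD) is applied to the primary measures, which are people linked to PrEP and people living with HIV linked to care, each per index person.

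Penetration into priority networks is assigned to secondary measures. The genetic one begins: "Among peers referred by all ambassadors, we will use a combination of study data, state HIV surveillance data, and molecular epidemiology". Table 1 lists it as "Proportion and number of peers living with HIV who are associated with a genetic cluster involving a new HIV diagnosis". According to Overview of Key Roles, peers enter through ambassadors, and ambassadors must live in the Charlotte region. The Figure 4 legend describes the intervention as a bundle: "D. eSNS, which combines all 3 strategies".

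**The concern.** The second hypothesis is specific. It has a comparator (partner services alone), a count, a population (people not yet diagnosed) and a criterion (closely related virus). The Introduction also names identification of transmission networks, including those marked by closely related infections, as one of two things whose effectiveness will be evaluated, so this is not a side remark.

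The measures assigned to it have no control value. The trial would report a Charlotte proportion, and a reader could take a high value as evidence that eSNS reached further than partner services. That proportion can also be high because ambassadors refer people whose HIV was already known and whose sequences already sit in a cluster. The one HIV measure that is compared between regions can move for reasons unrelated to undiagnosed infection, such as people with a known diagnosis being linked to care.

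**Working it through.** No arithmetic decides this point, so hypothesis and measures are set side by side.

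**The plan's own figure.** No target or power is given for the second hypothesis. The one power statement, under Sample Size and Power Estimates, concerns the network index. Its expected value reproduces: (80 index persons × 1.7 + 20 ambassadors × 5.0) / 80 = (136 + 100) / 80 = 2.95, stated as 3.0. That index counts contacts and peers. It says nothing about undiagnosed or genetically linked HIV.

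**What the hypothesis needs.** A measure must (a) exist in both regions, (b) count new diagnoses and (c) require close genetic relatedness.

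**What Table 1 offers.** It has 2 + 2 + 1 + 4 = 9 measures.

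| Measure | (a) Both regions | (b) New diagnosis | (c) Genetic linkage |
|---|---|---|---|
| People with HIV linked to care, per index case | yes | not required | not required |
| HIV-negative people linked to PrEP, per index case | yes | no | no |
| Peers with HIV associated with a genetic cluster | no | not required of the peer | yes |
| Peers with high bridging scores | no | no | not required |
| Previously diagnosed peers not virally suppressed, per ambassador | no | no | no |
| Newly diagnosed peers who start care | no | yes | no |
| Previously diagnosed peers who re-engage | no | no | no |
| Peers testing negative who start PrEP | no | no | no |
| Positivity among peers who test | no | largely | no |

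Two entries need a reason.

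- *Care linkage per index case.* The table row speaks of individuals diagnosed with HIV, and the text of Effectiveness Evaluation of individuals living with HIV. Neither limits the count to new diagnoses. Someone newly diagnosed but not linked to care would not count, and someone diagnosed earlier and now linked would.
- *Cluster measure.* The new diagnosis in its definition belongs to the cluster, not to the peer. A peer diagnosed earlier counts if the cluster contains somebody else's new diagnosis.

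**Result.** Two of nine measures meet (a), one clearly requires (c), and 0 of 9 meet (a), (b) and (c) together. The effective reproduction number, also mentioned under Effectiveness Evaluation, is not a count of people identified and does not fill the gap.

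**Attribution.** There are two regions. One receives the whole bundle and the other standard partner services. The contrast estimates the package, and no part of it separates cluster analysis from the social network component.

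**The case against.** Several replies have force.

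- *Raleigh does have an HIV measure.* People linked to care per index case is collected in both regions and partly overlaps the hypothesis. A reader might infer that nothing relevant is measured in Raleigh, and that would be wrong. What is absent is a Raleigh measure of newly diagnosed, genetically linked HIV.
- *No arm isolating cluster analysis is needed.* The hypothesis names partner services alone as its comparator, and Charlotte against Raleigh is that contrast. The lack of a third arm is not a flaw. It matters only because the wording credits cluster analysis with the gain.
- *The article is condensed and Table 1 is a selection.* A fuller document may define a further measure, and sequences are reported to the state. It would therefore go too far to say that the hypothesis cannot be tested. Still, the article itself says in prose how penetration will be assessed, and each of those measures is among peers.
- *Sequence data need not stop at Charlotte.* Data Sources and Management ties routine sequence analysis to cluster response in Region II, but the Results section mentions baseline molecular analyses across both states. The documents do not show that Raleigh sequences are out of reach.
- *Enrolment source and diagnosis status are partly handled.* The plan promises the same measures by source of ambassador and restricts the RPDD to those enrolled through partner services. Table 1 separates new from prior diagnoses in its care rows. Nor do the documents say that community-recruited ambassadors lack a link to an index person. The linkage measure itself, however, is stated across all ambassadors and is not split by diagnosis.

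These replies narrow the point but leave its core standing.

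**Conclusion.** The point stands in a limited form. As described, the plan does not test its second hypothesis, because no listed measure counts newly diagnosed, genetically linked people in both regions. The principal hypothesis, the primary measures, the RPDD and the power statement are unaffected.

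The gap is structural, at 0 of 9 listed measures, and the article gives no basis for sizing a bias. A reader might infer that most of the cluster measure's numerator would be people diagnosed earlier. The documents give neither the share of newly diagnosed peers nor the chance that new and prior diagnoses fall in a qualifying cluster, so no such share can be stated. What can be said is that prior diagnoses are eligible for the count.

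The conclusion rests on two readings: that peers arise only through ambassadors living in the Charlotte region, as the eligibility text says, and that the measures named for penetration are the ones intended for this hypothesis.

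**What to change.** 1. Add one secondary measure, computed identically in Charlotte and Raleigh from state surveillance and sequence data: the number of newly diagnosed contacts or peers whose virus meets the plan's genetic-linkage criterion, per eligible index person. In Charlotte, limit it to chains that start from partner services, as is already done for the RPDD.
2. Word the hypothesis as the eSNS package against partner services, without crediting cluster analysis separately.
3. Report the peer-only proportions as descriptive, split by new and prior diagnosis.
4. If Raleigh sequence data cannot be used, label the second hypothesis descriptive within Charlotte.

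The cost is running the planned sequence analysis on Region IV reports as well, plus changes of wording. The Results section reports that baseline molecular analyses were awaiting data sharing agreements, so the use of Raleigh sequences should be confirmed there. The drawback is precision: counts will be small and some genotypes missing, so the measure should carry an interval and not be presented as a powered test. Final results are expected in 2028, so the definition can be fixed before they are known.

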#### Effectiveness Evaluation

Intervention effectiveness will be assessed by comparing the 5-county Charlotte region to another urban North Carolina region, Raleigh, with similar demographics (see Figure 1). The metropolitan region surrounding Raleigh has the second-largest population in North Carolina, after Charlotte [47]. The primary effectiveness measures are the number of HIV-negative individuals linked to PrEP and the individuals living with HIV who are linked to care per index person from a priority network. Index persons in the intervention region (Charlotte) priority networks will be compared to index persons in the control region (Raleigh) priority networks, who receive standard-of-care partner services. Partner services are standardized among all North Carolina DHHS Field Service regions [48]. We will use a regression point displacement design (RPDD) [49] to assess the impact of eSNS on trends in our primary effectiveness measures between regions over the intervention period; the effective reproduction number for HIV will also be calculated over this period. Measures will be collected for each region at a preintervention baseline (2 years before), postintervention (6 months after), and during implementation for interim analyses at 6-month intervals. Because state HIV surveillance data is available in both the Charlotte and Raleigh regions from the baseline timepoint to a postintervention timepoint, RPDD provides statistical power to estimate the effect of eSNS when aggregating at a group level (index persons from priority networks) [50].

Although we adapted our original intervention design to enroll eSNS ambassadors through both routine partner services for index persons from priority networks and through ongoing waves of community-based recruitment, we will calculate the same effectiveness measures for ambassadors enrolled through each source. Only outcomes for ambassadors enrolled through partner services will be included in the RPDD analysis. However, for ambassadors enrolled through both sources, secondary effectiveness measures will also assess the extent to which eSNS penetrates priority networks where HIV transmission is ongoing. Among peers referred by all ambassadors, we will use a combination of study data, state HIV surveillance data, and molecular epidemiology to calculate the proportion of peers living with HIV that has close genetic linkages [42] to a cluster. We will also assess penetration into priority networks by calculating the proportion of newly diagnosed peers who initiate care, proportion of previously diagnosed peers who re-engage in care, the overall positivity among peers who test for HIV, and the proportion of peers testing negative who then initiate PrEP. Selected primary and secondary effectiveness measures are described in Table 1.

**Table 1. T1:** Selected effectiveness measures of the enhanced social network strategy (eSNS) intervention.

Measures and description		Data source
Network Index		
Number of individuals diagnosed with HIV and linked to care per associated index case.^a^		Surveillance data
Number of HIV-negative individuals linked to PrEP^b^ per associated index case.^a^		Surveillance data
Cluster analysis		
Proportion and number of peers living with HIV who are associated with a genetic cluster involving a new HIV diagnosis.		Study and surveillance data
Peers identified with high network bridging scores (betweenness centrality) [51].		Study and surveillance data
Viral suppression		
Number of peers per ambassador previously diagnosed with HIV who are not virally suppressed.		Study and surveillance data
Care and prevention linkage		
Proportion and number of peers newly diagnosed with HIV who initiate care.		Study data
Proportion and number of peers previously diagnosed with HIV who re-engage in care.		Study data
Proportion and number of peers who test negative and initiate PrEP.		Study data
Proportion of positive tests among all peers who test for HIV.		Study data

a Primary effectiveness measures.

b PrEP: pre-exposure prophylaxis.

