### Study Setting

The Carolinas RESPOND study focuses on North Carolina and South Carolina, with collaboration among academic and public health partners in both states (see Figure 1). The eSNS intervention described in this protocol is planned for the Charlotte region, covering a 5-county area in the North Carolina Department and Health and Human Services’ (DHHS) Field Services Region II, which includes the EHE priority jurisdiction [28] of Mecklenburg County (with star in Figure 1). This region directly borders the Midlands region of South Carolina, one of 7 US states with a disproportionate burden of HIV in rural areas [26]; the regions are connected by Interstate 77, which runs from Charlotte, North Carolina, to Columbia, South Carolina (see diamond in Figure 1). Although implementation is focused on the Charlotte region, our eSNS will follow networks that may cross both states because of Charlotte’s geospatial proximity to South Carolina. Due to comparable demographics and HIV epidemiology [27], North Carolina DHHS’s Field Services Region IV, the 11-county area surrounding the Raleigh, North Carolina metropolitan area, was chosen as a “control” region against which outcomes in the Charlotte, North Carolina “intervention” region will be compared.

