### Study Design

We designed a 3-phase process (see Figure 2) to develop, implement, and evaluate eSNS using a quasi-experimental, nonrandomized hybrid type 1 effectiveness-implementation design [34]. This design allows for evaluation of both eSNS effectiveness and the intervention delivery process. Phase 1 (preimplementation), which involved establishing a community advisory group and collecting mixed methods data to inform adaptations to SNS procedures, concluded in August 2024. Analyses of Phase 1 data, which are ongoing, aim to understand the structural, spatial, and network factors that influence HIV services engagement among the study’s priority groups, plus barriers and facilitators to eSNS implementation. In Phase 2, eSNS will be implemented in the Charlotte region over a 3-year period (2025‐2027). In Phase 3, we will evaluate the impact of eSNS on HIV services use compared to standard-of-care partner services delivered in the Raleigh, North Carolina metropolitan region [27] (see Figure 1).

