#### Sample Size and Power Estimates

Of approximately 280 new HIV diagnoses reported annually in the Charlotte region, 80 would meet criteria for index persons eligible to be assigned to DIS coaches for routine partner services (including 20 acute HIV infection). From these 80 index persons, we estimate that 25% of contact networks reached through partner services will yield an enrolled ambassador (n=20). Based on partner services data previously reported to North Carolina DHHS, 100 contacts were elicited from 60 persons who were newly diagnosed with HIV in the Charlotte region from 2016 to 2019, yielding a network index of 1.7 (SD 1.8). With a peer outreach network index of 5.0 per ambassador (based on previous reports [22]), this would increase the overall network index in the Charlotte region from 1.7 to 3.0. We estimate an 80% power with alpha=.05 to detect a significant effect of eSNS on network index with 20 ambassadors enrolled per year for 3 years (n=60). Of note, we do expect that ambassadors’ referral networks will have a bimodal distribution—with most having a low number of peers while a few will yield a high number of peers.

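### The primary RPDD is described with one treated and one control region, which cannot support an RPDD line, a standard error at region level, or the claim that the design supplies power

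*Protocol article*

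**What the plan says.** All places are in the protocol article.

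- **Design** (Study Design): the evaluation is built "using a quasi-experimental, nonrandomized hybrid type 1 effectiveness-implementation design".
- **Method** (Effectiveness Evaluation): "We will use a regression point displacement design (RPDD) [49] to assess the impact of eSNS on trends in our primary effectiveness measures between regions".
- **Units compared** (Effectiveness Evaluation): "Intervention effectiveness will be assessed by comparing the 5-county Charlotte region to another urban North Carolina region, Raleigh". The same section also says that index persons in Charlotte's priority networks are compared with those in Raleigh's.
- **Control** (Study Setting): "the 11-county area surrounding the Raleigh, North Carolina metropolitan area, was chosen as a" control region. The counties are described as its area and are not named as analysis units.
- **Measurement** (Effectiveness Evaluation): "Measures will be collected for each region at a preintervention baseline (2 years before), postintervention (6 months after" the intervention), with further collection every 6 months during delivery for interim analyses.
- **Power claim** (Effectiveness Evaluation): "RPDD provides statistical power to estimate the effect of eSNS when aggregating at a group level (index persons from priority networks").
- **Power figure** (Sample Size and Power Estimates): "We estimate an 80% power with alpha=.05 to detect a significant effect of eSNS on network index", with 20 ambassadors a year for 3 years (n=60), a network index rising from 1.7 to 3.0, and SD 1.8. No between-region variance is given.
- **Restriction** (Effectiveness Evaluation, second paragraph): only outcomes for ambassadors enrolled through partner services enter the RPDD. Raleigh, which receives standard partner services, has no ambassadors.

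**The concern.** In its standard form an RPDD regresses post values on pre values across several untreated units, then asks how far the treated unit lies from that line. The control units supply both the line and the residual variance against which the displacement is judged. A single control unit supplies neither.

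The article's remark that the group level consists of index persons suggests that replication might come from individuals. That changes the question. Index persons in one region and period share the same DIS staffing, PrEP access and local funding, and a person-level standard error does not reflect how much those conditions vary between regions over time.

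At stake is the primary effectiveness conclusion. It could rest on a test that cannot be computed as named, or on a p-value that is too small because the region-level component was left out.

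**Working it through.** **1. The plan's own power figure.** Inputs from Sample Size and Power Estimates: 80 index persons and 20 ambassadors a year, baseline network index 1.7 (SD 1.8, from 60 persons), 5.0 peers per ambassador.

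- Effect: (80 × 1.7 + 20 × 5.0)/80 = 2.95, about 3.0. Difference 3.0 - 1.7 = 1.3.
- Power, with persons independent and a two-sided 5% test: Φ(1.3/[1.8 × √(1/n1 + 1/n2)] - 1.96). Sidedness is not stated.
  - 30 vs 30 (60 in total): √(1/30 + 1/30) = 0.258, ratio 2.80, power 79.9%.
  - 60 historical persons vs 20 ambassadors: √(1/60 + 1/20) = 0.258, power 79.9%.
  - Other readings: 80 vs 20, 82.4%; 60 vs 60, 97.7%; 20 vs 20, 62.7%; one-sided 30 vs 30, 87.5%; one-sample n=60, above 99.9%.

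The readings that return 80% from the stated inputs alone are two-sample tests on independent persons. An unstated design effect of about 2 (ICC about 0.017) would also bring 60 vs 60 down to 80%, but the article mentions no such allowance.

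**2. RPDD with region as the unit.** Model: post = a + b × pre + d × treated.

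- Points: 2 (Charlotte, Raleigh). Parameters: 3. Rank 2, residual df = 2 - 3 = -1.
- Fixing the slope b at 1 leaves 2 parameters and 2 points: residual df 0, still no variance estimate.
- Stacking the repeated follow-ups does not help. With 7 per region (assumed: six half-yearly points over 3 years plus one post point) on one baseline value per region, the columns intercept, pre, treated and time number 4 but have rank 3, because pre and treated are aliased.

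**3. Index persons as the unit.** eSNS Intervention Overview gives preference to acute infection and to chronic infection under age 30, and adds virally unsuppressed cluster members. Most index persons are therefore newly diagnosed, and those counted at baseline are largely different people from those counted later. Without paired pre-values there is no pre-post line.

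A person-level test is still computable. Its true two-sided error, if a region-by-period component exists, is 2 × [1 - Φ(1.96/√DE)], with DE = 1 + (n - 1) × ICC. The ICC is assumed. The n per region is 60 (planned ambassadors) or 240 (80 × 3 Charlotte index persons), with an equal Raleigh number assumed.

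| ICC (assumed) | n = 60: DE, true alpha | n = 240: DE, true alpha |
|---|---|---|
| 0 | 1.00, 5% | 1.00, 5% |
| 0.01 | 1.59, 12% | 3.39, 29% |
| 0.02 | 2.18, 18% | 5.78, 41% |
| 0.05 | 3.95, 32% | 12.95, 59% |

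**4. What more control points would give.** With one treated point and k controls, residual df = (k + 1) - 3 = k - 2. The smallest displacement detectable with 80% power is about √(1 + 1/k) × (t0.975 + t0.80), in residual SDs. This is a best case: Charlotte's pre-value at the control mean and equal variance at all points.

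| k | df | t-critical | Detectable (residual SDs) |
|---|---|---|---|
| 1 | -1 | none | none |
| 2 | 0 | none | none |
| 3 | 1 | 12.7 | 16.3 |
| 5 | 3 | 3.18 | 4.6 |
| 11 | 9 | 2.26 | 3.3 |

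**The case against.** The strongest reply is that the article never writes out the model or the number of RPDD points. The unit could be the region, the county or the priority network, and the SAP, which is not shown, may settle it. This stands in part: non-identifiability follows only if the region is the unit, and a reader who infers that no standard error of any kind can exist goes further than the text. It does not rescue the stated plan. The article names one control region, collects measures by region, and asserts that the design supplies power. None of its readings yields both an RPDD and a standard error that covers region-level variation unless units it does not name are used.

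Several further inferences are tempting but unsupported:

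- **A single baseline value that rules out any check of pre-trends.** The 2-year baseline may be a window, and surveillance data are said to be available throughout. How it is binned is a point to clarify.
- **A post window that discards delivery-period data.** The same section says trends over the intervention period are assessed. This too needs clarifying and is not an error.
- **Charlotte's EHE priority status as a confounding change.** It is a pre-existing feature. Only changes over time that flow from it, such as funding, would matter.
- **59% as the size of the problem.** That is the upper end of an assumed ICC range at the larger assumed n.

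It is also fair to say that confounding with region is inherent in an openly nonrandomized design, and that Raleigh was chosen for comparable epidemiology. That explains the choice of comparator but does not supply the missing replication.

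**Conclusion.** The point holds in bounded form. As described, the primary RPDD has one control point. With region as the unit it cannot be estimated (residual df -1). With persons or networks as the unit it yields a standard error, but one that omits region-by-period variation, and the analysis is not the named design.

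The statement that RPDD provides statistical power is therefore unsupported, and the 80% is best read as a person-level figure with no between-region variance. The extent of type I error inflation is uncertain: about 12% to 32% at 60 per region and 29% to 59% at 240, for assumed ICCs of 0.01 to 0.05 and an assumed equal Raleigh count. It vanishes only if the region-by-period component is zero, which two regions cannot show. Because this is the primary effectiveness analysis, it should be settled before the final analysis.

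**What to change.** 1. **Name the RPDD units and use several control points.** The preferred source is the other North Carolina Field Services Regions, if data access allows, since "Partner services are standardized among all North Carolina DHHS Field Service regions". Otherwise, or in addition, use the 11 Region IV counties, weighted by number of index persons. Test the pooled Charlotte point against the residual variance of the control points; 11 controls give 9 residual df.
2. **Correct the power statement.** Withdraw the sentence crediting RPDD with power, or recompute power at the level of the control points (best case about 3.3 residual SDs with 11 controls). Present the 80% as a person-level figure that excludes region-level variation.
3. **Reclassify the pooled contrast.** Report Charlotte versus Raleigh as descriptive, or name a different model, such as difference-in-differences over the 6-month points, and state its assumption that nothing else changed in one region only.
4. **Clarify** how the 2-year baseline is binned and which period the post value covers.

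Cost: revised analysis text, a finer cut of surveillance data for the county option, and possibly a wider data agreement for other regions, whose availability the article does not establish. Intervals will be wider and small counties will give noisy points. County controls within one region capture between-county variation there; they do not remove confounding by a change that affects Charlotte alone, and this should be stated as a limitation.
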